### Randomization and Blinding

Data analysis will be conducted independently of cohort recruitment and follow-up. The evaluation of data will take place at the Deusto Institute of Technology (Ultrasound Data Evaluation Center) and Biodonostia (Blood-based Assays Evaluation Center). Initially, only anonymized data, including ultrasound images, raw data, and blood-based assays, will be transmitted to the data evaluation centers. In the case of combination models, a training set of clinical variables will also be transferred to the data evaluation centers. Reserved data sets will be kept at the clinical acquisition centers for independent testing. This includes data from various sites and information obtained during follow-up examinations.

### Outcomes

#### Primary Outcomes

Investigating the association between quantitative ultrasound biomarkers related to muscle mass and quality (thickness [mm], cross-sectional area [cm^2^], perimeter [mm], pennation angle [degrees]) extracted from raw data and blood-based biomarkers, as well as their combinations with clinical variables. These clinical variables encompass frailty (FRAIL [short 5-question assessment of Fatigue, Resistance, Aerobic capacity, Illnesses, and Loss of weight] scale ranging from 0 to 5, with 0 indicating robustness and 5 indicating frailty, and Frailty phenotype by Fried et al [4], ranging from 0 [robust] to 5 [frail]), sarcopenia (SARC-F [Strength, Assistance with walking, Rising from a chair, Climbing stairs, and Falls] scale scores ranging from 0 [robust] to 10 [sarcopenic]), physical function (Short Physical Performance Battery [SPPB] Scale score ranging from 0 to 12, where 0 indicates the lowest physical performance and 12 indicates the highest performance), International Physical Activity Questionnaire scores ranging from 0 (lowest) to 3 (highest), Gait Speed Test in seconds, grip strength measured by Jamar dynamometer in kilogram, disability (Global Deterioration Scale, consisting of 7 stages), Barthel Index (ranging from 0 [total dependent] to 100 [independent]), Lawton and Brody Index (scores from 0 [dependent] to 8 [independent]), nutritional status (Mini Nutritional Assessment—Short Form), body composition (DXA), and quality of life (EQ-5D-5L) within 3 cohorts of older adults: hospital control cohort, hospital exercise cohort, and primary care cohort.

#### Secondary Outcomes

In the hospital exercise cohort, we will assess changes in quantitative ultrasound and blood-based biomarkers, as well as clinical variables, following a 16-week multicomponent physical exercise program. Additionally, exploring associations between ultrasound and blood-based biomarkers and the remaining clinical variables both before and after the exercise program.In the hospital control cohort, we will examine changes in quantitative ultrasound and blood-based biomarkers, along with clinical variables, following a 16-week follow-up period without intervention. Furthermore, we will explore associations between quantitative ultrasound and blood-based biomarkers and the remaining clinical variables after the 16-week follow-up period.In the primary care cohort, we will assess changes in quantitative ultrasound and blood-based biomarkers, along with clinical variables, following a 1-year follow-up period without intervention. Additionally, we will explore associations between quantitative ultrasound and blood-based biomarkers and the remaining clinical variables after the 1-year follow-up.We will evaluate differences in the changes of all measurements among the 3 cohorts. A direct comparison will be made between the 2 hospital cohorts, while the primary care cohort will serve as a reference for understanding changes in nonhospital populations.

### Outcome Measurements

The list of clinical variables collected at baseline and follow-up assessments is included in Textbox 2.

Clinical variables in baseline and follow-up examination.Global Deterioration Scale of Reisberg for assessment of cognitive function.Charlson Comorbidity Index.Barthel Index of independence to perform basic activities of daily living.Lawton and Brody Index of independence to perform instrumental activities of daily living.Short Physical Performance Battery for Physical Function Assessment.SARC-F (Strength, Assistance with walking, Rising from a chair, Climbing stairs, and Falls) scale of sarcopenia screening.FRAIL (short 5-question assessment of Fatigue, Resistance, Aerobic capacity, Illnesses, and Loss of weight) scale of frailty evaluation.Frailty phenotype of frailty proposed and validated by Fried et al [4].Mini Nutritional Assessment—Short Form for nutritional screening.International Physical Activity Questionnaire for physical activity levels.EQ-5D-5L for health-related quality of life assessment.Gait Speed Test for Physical Function Assessment.Grip strength with Jamar dynamometer.Population characteristics: age, sex, and BMI.Body composition (dual-energy X-ray absorptiometry; total muscle mass, appendicular lean soft tissue mass [ALM], dual-energy X-ray absorptiometry [ALM/h^2^ or ALM divided by height squared], total fat, and fat percentage)

### Ultrasound Imaging and Raw Data Acquisition

The ultrasound equipment used in this study is the L7 HD3 portable linear scanner (Clarius Mobile Health Corp.). Specifically designed for point-of-care ultrasound examinations, the probe of this device boasts a frequency range of 4-13 MHz with a center frequency of 7 MHz. To facilitate seamless data transfer, anonymized digital ultrasound data are transmitted from the scanner through a customized Wi-Fi network to a smart device, enabling real-time B-mode navigation and data storage. The important feature of the scanner is an integrated image processing package designed to optimize B-mode musculoskeletal image quality. This technology enhances the clarity and quality of musculoskeletal imaging during examinations. Additionally, the scanner is equipped with a research package designed to capture raw beamformed backscattering ultrasound data after the beamformer. These raw data are presented in an in-phase/quadrature complex baseband representation, commonly referred to as IQ data. The IQ data serve as the foundation for the implementation of tailored quantitative ultrasound algorithms [71].

All examinations will be conducted within a depth range of 0-60 mm, using 50% of the maximum acoustic output offered by the scanner. During measurements, efforts will be made to minimize skin-probe compression to maintain acceptable image quality. Following each examination, the acquired data will be uploaded to a HIPAA (Health Insurance Portability and Accountability Act)-compliant cloud service, offered by the scanner’s manufacturer, enabling the centralization of data (Figure 3).

**Figure 3 figure3:**
[figure not shown]
Ultrasound data flow and management from clinical acquisition centers to ultrasound data evaluation center.

### Ultrasound Examination Protocol

The midpoint of the thigh will be determined and marked as the half-distance between the superior border of the patella and the anterior-superior iliac crest. Using the femur as a guide in the transverse view, the midpoint of each thigh will be located, and the various components of the quadriceps muscles (rectus femoris, vastus intermedius, vastus medialis, and vastus lateralis) will be identified (Figure 4).

**Figure 4 figure4:**
[figure not shown]
Echographic B-mode appearance of mid-thigh in the (A) transverse and (B) longitudinal views.

In each examination, a minimum of 12 coregistered B-scan and raw data frames will be obtained. This will include 3 transverse and 3 longitudinal views for both thighs. The longitudinal examination will be conducted in a plane where fasciculations are visible, ensuring comprehensive coverage and detailed assessment of the musculoskeletal structures.

### Evaluation of Quantitative Ultrasound Biomarkers

#### Morphometric Ultrasound Measures

Throughout the examination, the sonographer will record morphometric ultrasound measurements using the online ultrasound scanner’s interface (Figure 5). This includes capturing the thickness of the rectus femoris in the transverse view at the midsection point, measuring the perimeter and cross-sectional area of the rectus femoris in the transverse view, and determining the pennation angle in the longitudinal view.

**Figure 5 figure5:**
[figure not shown]
Morphometric ultrasound measurements. (A) Rectus femoris thickness, cross-sectional surface, and perimeter (transverse view). (B) Pennation angle (longitudinal view).

#### Raw Data Evaluation

Quantitative ultrasound biomarkers will be assessed offline using the acquired raw IQ data. Regions of interest encompassing the rectus femoris will be delineated in the raw data domain by automatically generating B-mode images from the raw data. This process will use the coregistered clinical B-mode images and sonographer annotations as a reference for the definition of the accurate region of interest. Table 1 presents a list of state-of-the-art quantitative ultrasound biomarkers, the hyperparameters of which will be systematically adjusted through experimental adaptation for musculoskeletal examinations. These adjustments will be made and subsequently evaluated using the raw data obtained from the ultrasound probes during the study.

**Table 1 table1:** Quantitative ultrasound biomarkers based on raw data.

Biomarker	Description	Literature references
Automatic morphometric measurements	Automatic muscle morphometric analysis based on neural network segmentation models trained with respect to sonographer annotations of rectus femoris cross section, and 2D Fourier analysis of pennation angle.	[72,73]
Attenuation coefficient	Measurement of loss of signal intensity with depth.	[47,48,50]
Backscattering coefficient	Measurement of tissue reflectivity after attenuation compensation.	[74,75]
Power spectrum (Lizzi-Feleppa parameters)	Spectroscopy measurement of backscattered signal variation with frequency, including parametrizations such as spectral slope, spectral intercept, and midband fit	[49]
Speckle statistics	Fitting of raw envelope signal to speckle statistical distribution models, including Rayleigh, Nakagami, and homodyned K-distribution. Estimation of scatterer concentration, spacing, and coherence from fitted model parameters.	[49,76,77]
Statistical moments	Nonparametric statistical moments capturing scatterer distribution and concentration, such as entropy, kurtosis, skewness, variance, anisotropy, and signal-to-noise ratio.	[78,79]
Coherence and speed of sound	Generalized spectrum analysis and estimation of coherence, mean scatterer spacing, and speed-of-sound in muscle.	[80,81]
Textural radiomics	First- and second-order texture features extracted from both B-mode (eg, based on gray-scale co-occurrence matrices) and raw data (eg, based on wavelet and Laplacian transformations) and combined with machine learning models trained with respect to clinical outcomes.	[51,53,54]
Artificial intelligence radiomics	Radiofrequency data and B-mode features extracted automatically with end-to-end neural network models trained with respect to clinical outcomes	[52,82-84]

### Evaluation of Blood-Based Biomarkers

During both basal and follow-up acquisitions, venipuncture will be performed to collect one 10-mL serum blood tube and two 5-mL ethylenediaminetetraacetic acid (EDTA) blood tubes. The serum sample will undergo centrifugation and will be stored in 4 aliquots. One of the EDTA samples will be promptly frozen and stored at –80°C, while the other will be subjected to centrifugation for plasma and buffy coat extraction. These samples will be stored at –80°C at the clinical sites until transportation, which will be carried out with dry ice to the Blood-Assay Evaluation Center for subsequent processing and storage (Figure 6).

The expression of previously described biomarkers, including vitamin D, lutein zeaxanthin, troponin T, pro-brain natriuretic peptide, soluble receptor for advanced glycation end products (sRAGE) [85], and microRNAs, along with those associated with relevant pathways related to frailty such as inflammation (interleukin 6) and senescence (p16INK4A and p21CIP [56]), will be assessed in cells obtained from a blood sample. This evaluation will be conducted in a subsample of patients in baseline conditions and after intervention at both the transcriptional and protein levels, as outlined in Table 2. Erythrocytes will be lysed using Buffer EL (Qiagen), and total RNA from leukocytes will be isolated using the miRNeasy Mini Kit (Qiagen). Initially, RNA samples will undergo purification with the RNeasy Kit (Qiagen). Subsequently, the RNA will be retro-transcribed, and gene expressions will be quantified through quantitative polymerase chain reaction (PCR) using specific primers or probes and the ABI Prism SDS 7300 Real-Time PCR System (Applied Biosystems). Expression levels will be normalized to the expression of the enzyme glyceraldehyde-3-phosphate dehydrogenase (GAPDH) [86]. Furthermore, protein levels will be assessed in serum samples using Quantikine enzyme-linked immunosorbent assays and Luminex, as previously outlined [87].

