**Results:**

At the time of manuscript submission, the enrollment of volunteers is ongoing. Recruitment started on March 1, 2022, and ends on June 30, 2024.

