#### Primary Care Cohort

Participants will be consecutively recruited from the scheduled patient list of the primary care units. Upon obtaining informed consent, baseline study variables will be collected. These patients will be followed up for 1 year under usual care. After the 1-year follow-up, a repetition of the baseline evaluation will be conducted.

Recruitment is conducted by the study coordinator staff at each site, under the overall supervision of the clinical principal investigator at each site. Participants will sign the informed consent at the beginning of the first visit. The professional overseeing the assessment will provide an explanation of the project, and the participant will sign both the information sheet and the informed consent to participate. The principal investigator at each site will be responsible for collecting and monitoring the documentation related to informed consent. The inclusion and exclusion criteria are listed in Textbox 1.

Inclusion, exclusion, and termination criteria.

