### Interventions

In the hospital exercise cohort, a 16-week supervised multicomponent physical exercise program will be implemented. The individualized exercise intervention, tailored to each individual’s functional capacity, comorbidities, and previous experience, will consist of 2 supervised sessions per week, each lasting 45 minutes. These sessions will be conducted in small groups, with 4-6 older adults per group. The sessions are divided into warm-up, main part (strength, power, and coordination exercises), and cool down (flexibility and stretching). The main part of the exercise program comprises 8 exercises targeting the major muscle groups. The progression starts with low-intensity and high-volume sessions, gradually advancing to higher intensities and lower volumes. Depending on the stage, participants will complete 2-4 sets, consisting of 4-15 repetitions, with a 30-second rest between sets and exercises. For each exercise, loads and intensities will be adjusted to achieve a total of 30 repetitions. All exercise sessions are to be conducted in the gym of the Geriatrics Department of the hospital. Participants will be encouraged to incorporate additional 90-minute walks per week into their routine. It is important to note that the exercise program is aligned with the guidelines of the VIVIFRAIL program [67], which specifically aims to prevent weakness and reduce the risk of falls.

In the hospital control and primary care cohorts, no specific intervention will be implemented.

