### Statistical Analysis

The study population will be characterized based on demographic and clinical attributes. Categorical data will be summarized with frequency and percentage representations. Continuous data will be described using mean, SD, median, and the 25th and 75th percentiles. Furthermore, the distribution of ultrasound parameters with respect to the primary endpoint will be depicted using graphical techniques. The correlation of quantitative biomarkers will be evaluated for each multifactorial clinical evaluation parameter using the Pearson correlation coefficient for continuous variables and the Spearman correlation coefficient for categorical variables [88]. Unpaired tests, such as the Student *t* test, will be used for comparing means of biomarkers among various acquired patient cohorts and for stratified patient subgroups based on the frailty scales outlined in Textbox 1. To manage the extensive array of ultrasound and blood biomarkers, a robust statistical analysis plan will be implemented. This plan will incorporate correction methods to address the risk of type I errors associated with multiple comparisons. Specifically, for the primary outcome concerning biomarker-clinical associations, we will use Lasso regression. This technique automates the selection of relevant variables, reducing the necessity for extensive corrections and improving interpretability. Paired statistics will be applied in the statistical analysis for longitudinal monitoring, encompassing both interventions and clinical follow-up. The monitoring period in hospital and primary care environments will differ to accommodate the distinct follow-up workflows in each setting. The duration of primary care follow-up aligns with established norms [89,90]. To account for differences in follow-up duration among cohorts over time, our data analysis will incorporate appropriate statistical methods, potentially enabling adjustments for these variations. For the secondary objective, the impact of physical intervention in 50 patients will be compared with 50 patients with no intervention. With 80% power, the planned population size will enable the detection of a biomarker with a medium effect size of E/S=0.284 at a 2-sided α level of .05.

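### Change in vitamin D (and possibly physical activity) over 16 weeks is tested within cohorts and set beside a 1-year reference without a season term or calendar matching, so it can include seasonal drift; the direct hospital contrast is largely protected.

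*Protocol article*

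**What the plan says.** Vitamin D is in the blood panel, which is described as "including vitamin D, lutein zeaxanthin, troponin T, pro-brain natriuretic peptide" and further markers (Evaluation of Blood-Based Biomarkers; Table 2). The same section says of the panel: "This evaluation will be conducted in a subsample of patients in baseline conditions and after intervention". The size of that subsample is not given. Physical activity is recorded at both visits: "International Physical Activity Questionnaire for physical activity levels" (Outcome Measurements, Textbox 2).

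The intervals differ by cohort. For the exercisers, "In the hospital exercise cohort, a 16-week supervised multicomponent physical exercise program will be implemented", with re-measurement when it ends. The hospital controls have the same 16-week interval under usual care. For primary care, "These patients will be followed up for 1 year under usual care".

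On analysis, "Paired statistics will be applied in the statistical analysis for longitudinal monitoring" (Statistical Analysis). Secondary Outcomes adds a comparison of changes among the three cohorts: the two hospitals directly, and primary care as a reference. The nearest provisions to a season adjustment are a conditional allowance for different follow-up durations, regression on covariates that are not named, and a post hoc look at population characteristics by centre (Limitations).

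On timing, "Recruitment started on March 1, 2022, and ends on June 30, 2024" (Abstract, Results). Allocation is by institution, and each site enrols from its own clinical agenda until its target is met. Nothing aligns calendar time between sites.

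**The concern.** Vitamin D depends on sun exposure, and outdoor activity may also vary over the year. A participant re-measured after 16 weeks is at a different point in the yearly cycle; one re-measured after a year is back at the same point. A paired test in a 16-week cohort cannot separate an effect of exercise from the season in which participants happened to start. The primary care reference carries almost no seasonal shift by design, so it can differ from both hospital cohorts for a reason unrelated to setting. The planned allowance for follow-up duration would not remove this, because seasonal drift is cyclic and not proportional to elapsed time.

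What is at stake is interpretation. The study wants to know whether its biomarkers respond to exercise, and a seasonal change in vitamin D could be taken for such a response.

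**Working it through.** The article states no figure on season, so there is none to reproduce.

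**Inputs from the article:** intervals of 16 weeks and 1 year; 50 exercisers and 50 hospital controls; recruitment from 1 March 2022 to 30 June 2024, which is 28 months; exercise sessions in groups of 4-6.

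**Assumed inputs:** a yearly sinusoid of half-range A; a late-August peak where a direction is needed; A = 0.25, 0.5 or 1 SD of individual change in the simulations.

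**1. Largest shift for one person.** Over a gap that is a fraction f of a year, the shift is at most 2A·sin(πf).
- 16 weeks: f = 16/52 = 0.31, and 2·sin(π·16/52) = 1.646, so up to 1.65A in either direction. This is 1.646/2 = 82% of the peak-to-trough swing.
- 1 year: 2·sin(π) = 0. A visit at exactly 52 weeks gives about 0.02A.

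**2. Net drift under even accrual.** Over whole years, drifts average to zero. The 28 months are two full years plus four extra months, March to June. With a late-August peak, the mean 16-week change for March-June starts is about 1.16A to 1.18A, depending on the exact peak day. Multiplied by 4/28, this is about +0.17A for a 16-week cohort. For A between 0.25 and 1 SD that is 0.04 to 0.17 SD.

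**3. False-positive rates with no exercise effect** (3,000 simulated studies per setting, 50 versus 50, nominal 0.05, random starts over 28 months unless stated):

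| Test and start pattern | A = 0.25 | A = 0.5 | A = 1 |
|---|---|---|---|
| Paired test, exercisers, individual starts | 0.06 | 0.08 | 0.13 |
| Paired test, exercisers, 10 common starts of 5 | 0.09 | 0.21 | 0.34 |
| Hospital contrast, individual starts | 0.06 | 0.05 | 0.04 |
| Hospital contrast, 10 common exercise starts | 0.08 | 0.12 | 0.21 |
| Hospital contrast, control dates matched to grouped exercise starts | 0.044 | 0.024 | 0.003 |
| Hospital contrast, hospitals in adjacent 3-month windows | 0.43 | 0.75 | 0.86 |

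With matched dates the hospital contrast is not inflated, but the paired test in exercisers alone still is (0.10, 0.21, 0.35). The grouped and adjacent-window rows are what-if cases; the article describes neither pattern.

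**4. Form of the season term.** At a fixed 16-week gap, the sine and cosine at follow-up are exact linear combinations of those at baseline. Four separate terms therefore have rank 2. The two follow-up-minus-baseline differences carry the same information without collinearity, and they are about zero for a 1-year gap, as they should be.

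**The case against.** **Season may be handled in a plan that is not shown.** The article promises a statistical analysis plan and regression on covariates. The lack of a named season covariate is therefore weak evidence, and no sentence in the article is wrong. This stands in part. The unequal intervals and the unmatched enrolment are design features that the article does state, and the paired tests, run as described, can absorb drift.

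**A reader might infer that nothing controls for season.** The article does not support that. The usual-care hospital cohort has the same 16-week interval and is the direct comparator. Seasonal drift cancels in that contrast as far as the two hospitals enrol over the same months, and one recruitment window is given for the whole study.

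**A reader might also infer that exercisers start in a few batches**, from "These sessions will be conducted in small groups, with 4-6 older adults per group". With 50 people that would be 9 to 12 groups (50/6 = 8.3; 50/4 = 12.5). But the sentence fixes the size of a session group, not common start or measurement dates. Recruitment is consecutive, and the baseline evaluation follows consent and precedes enrolment in the programme. Results that rest on grouped starts are conditional.

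**The scope is narrow.** Vitamin D is one of 12 rows in Table 2, assayed in a subsample, for a secondary outcome of a study that calls itself exploratory. The primary objective is cross-sectional, so this change-score argument does not reach it. The 16-week versus 1-year difference is acknowledged as a limitation, though without its seasonal consequence. All of this stands and limits the weight of the point. The subsample also means that start dates would average out less well than in the 50-versus-50 simulations.

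**Conclusion.** The point holds as an inexpensive improvement, not as an error in the plan. Two comparisons are exposed: the within-cohort 16-week change, and the comparison of either hospital cohort with primary care. One person's level can shift by up to 1.65A over 16 weeks and by about 0 over a year. A cohort accrued evenly over the 28 months would carry a net drift of only about 0.17A. The paired test in exercisers is mildly inflated with individual starts (0.06 to 0.13) and more so only if starts cluster.

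The direct exercise-versus-control contrast is largely protected. It is biased only if start dates differ between the hospitals, including through clustered exercise starts, and the article neither states nor excludes this.

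All sizes depend on an assumed sinusoid, amplitude and peak date, none of which is in the article. For physical activity the point is tentative: the questionnaire is scored 0 to 3, and nothing here quantifies its seasonality.

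**What to change.** - In the change analyses of vitamin D, and of physical activity if wanted, add two covariates: the follow-up-minus-baseline difference in the sine of day of year, and the same for the cosine. Do not enter separate terms for both visits. Show results with and without the two terms.
- Report the distribution of start dates by cohort, so that a reader can judge how far the hospitals overlap in calendar time.
- Rest any inference about exercise on the concurrent contrast between the two hospital cohorts.
- Do not credit unadjusted within-cohort changes, or hospital-versus-primary-care differences in vitamin D change, to exercise or setting.

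The cost is two degrees of freedom per model, which matters more if the assayed subsample is small. Visit dates must be in the database; the article's description of the database does not name them, so this needs checking. If starts in a cohort fall mostly in one season, the terms cannot cleanly separate season from the average change, and the start-date report will show that.
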